### 4.8. Data Analysis and Management

All collected data will be cleaned, coded, and entered into the computer. The anonymized data will be uploaded to a cloud server for storage. Access to this data store will be password protected. The data collected from the study will be stored on faculty One-drive cloud servers. After data collection, data from the entire study will be retrieved from the One-drive and downloaded as an Excel file (Microsoft Office, Redmond, WA, USA). Data analysis will be performed using the SPSS 23 (IBM, New York, NY, USA).

The descriptive parameters will be reported as mean values ± standard deviations (SD) and 95% of the confidence interval (95% CI). Data will be assessed for normality and homogeneity to ensure that the analysis’ assumptions will be met, using the Shapiro–Wilk test, Levene’s test, visual check of histograms, and Q–Q plots.

A one-way ANOVA with Bonferroni post hoc correction will be used to determine differences between the groups in all measured parameters. Additionally, Cohen’s d effect size (ES) will be used to calculate between-group differences and will be interpreted using the following thresholds: 0–0.2 was trivial, 0.2–0.6 small, 0.6–1.2 moderate, 1.2–2.0 large, 2.0–4.0 very large, and >4.0 extremely large effect [42].

Association analyses will be performed using the Pearson product–moment correlation coefficient. The strength of the relationship was determined using the following criteria: 0.1, small; 0.3, moderate; 0.5, large; 0.7, very large; 0.9, nearly perfect > 0.9 [43].

The results will be considered significant for values of <0.05.

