One of the well-studied and crucial peripheral factors, associated with the decline in CRF even in master athletes in their advanced age, is an age-related alteration in the skeletal muscle, which is likely a multifactorial process with a network of interacting malfunctional systems resulting in the accelerated loss of muscle mass, and a reduction in muscle strength and power [14,15,16]. This process is well known as sarcopenia. Several recent research studies showed that muscle-related alterations might be caused by factors such as central and peripheral nerve dysfunction and variations, the decrease and remodeling of motor units, fat and connective tissue infiltration, and the reduction and remodeling modifications in the cross-sectional muscle area (type II. muscle fibers reduction compared to type I. muscle fibers, and possible reinnervation) [16,17,18,19]. This multifactorial process is associated with complex structural and functional changes on the cellular level of the muscle fibers, such as a reduced satellite cells content, myonuclear number, capillarization, or mitochondrial dysfunction [16,20]. Likewise, on the subcellular and molecular levels, for example, dysfunction in EC coupling, loss and misplacement of mitochondria, and SOCE impairment have all been described within ageing. Altogether these alterations are accompanied by a development of low-grade chronic inflammation (inflammaging) [21,22].

Another factor which affects CRF is malnutrition caused by prolonged inadequate energy and/or protein intake [23,24]. In athletes, a relative energy deficiency is defined as “impaired physiological functioning caused by a relative energy deficiency and includes but is not limited to impairments of metabolic rate, menstrual function, bone health, immunity, protein synthesis, and cardiovascular health” [25]. From the aging perspective, the relative energy deficiency may negatively affect bone health and might increase the risks of osteoporosis development, which might be associated with higher risks of several fractures and injuries in the higher age of both elderly and master athletes [26,27].

The study primarily aims to investigate the benefits, and possible negative effects, of lifelong endurance training in master athletes, who actively run marathons, and compare these with elderly and young counterparts, who are less active than recommended by the WHO [5], as well as with young endurance trained athletes, who also run marathons.

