Therefore, based on the evidence, the specific objectives of the study are: To examine the (a) cardiorespiratory fitness, (b) skeletal muscle structural and functional, (c) inflammatory, (d) bone health, and (e) nutritional intake parameters.To determine the effects of aging and the physical activity level on the measured parameters.To describe the relationship between the ageing and physical activity level with monitored parameters.To identify the health benefits, and possible negative effects, of lifelong one-sided endurance training.

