## 2. Materials and Methods

### 2.1. Study Design

A descriptive cross-sectional study design is used among the four groups of participants. The study has been planned to be conducted from September 2021 due to gradual realization of some testing procedures.. The study protocol is designed based on SPIRIT Guidelines, and carefully described by using the SPIRIT checklist of items to be included in reports of cross-sectional studies.

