### 2.3. Sample Size

Based on the pilot study, with a mean effect size and a power of 0.9, the sample size of 14 participants per group would be needed to obtain a significant result. However, we will hire 20 subjects per group (in total, 80 subjects) to eliminate potential risks of drop out on the study outcomes. Sample size was calculated using G * Power 3.1.9.2 software.

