## 3. The Primary Outcome

The primary outcome measurements will be represented by the VO_2peak_ reached in the cardiorespiratory fitness testing on the cycle ergometer, as these parameters define the physical fitness level for each subject.

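### Single-step Bonferroni over the pairwise group comparisons gives up power that Holm's step-down would keep at the same 5% family-wise error

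*Protocol article*

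**What the plan says.** All references are to the protocol article. The Introduction gives the primary aim: "The study primarily aims to investigate the benefits, and possible negative effects, of lifelong endurance training in master athletes". It then says the study will "compare these with elderly and young counterparts, who are less active than recommended by the WHO [5], as well as with young endurance trained athletes". With master athletes as MA, young athletes as YA, young sedentary as YS and elderly sedentary as ES, that is three contrasts: MA-ES, MA-YS and MA-YA.

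The Introduction also lists specific objectives, one of which is: "To determine the effects of aging and the physical activity level on the measured parameters".

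Section 2.1 describes the design: "A descriptive cross-sectional study design is used among the four groups of participants". Section 3 sets the primary outcome without attaching a group contrast to it: "The primary outcome measurements will be represented by the VO_2peak_ reached in the cardiorespiratory fitness testing on the cycle ergometer".

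Section 4.8 fixes the test and the multiplicity rule: "A one-way ANOVA with Bonferroni post hoc correction will be used to determine differences between the groups in all measured parameters". On the significance level it says: "The results will be considered significant for values of <0.05". It does not list the pairs or give their number. It also plans Cohen's d for the group differences, with 0.6 to 1.2 labelled moderate.

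**The concern.** With four groups and no selected pairs, Bonferroni divides 0.05 by six. Each contrast that answers the primary aim is then tested at 0.0083, and stays at 0.0083 even after other pairs have clearly been rejected. In this design several differences may well be large, for example young runners with a 10 km best under 35 minutes against men with no training history. A single-step rule gains nothing from those clear rejections.

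What is at stake is sensitivity, not false positives. The study looks for benefits and for possible harms in master athletes across many parameters, with 20 men per group. A real difference in the range that 4.8 itself calls moderate could be reported as non-significant when a rule with the same error guarantee would have found it. This matters more for parameters with moderate differences than for any in which the groups lie far apart.

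**Working it through.** **1. The plan's own figure.** Section 2.3 gives the requirement: "Based on the pilot study, with a mean effect size and a power of 0.9, the sample size of 14 participants per group would be" (quotation cut here). Recruitment is 20 per group. The effect size has no number and neither test nor contrast is named, so 14 cannot be reproduced, only solved backwards at 90% power:
- four-group F-test at 0.05: 14 per group needs f = 0.522;
- two-sided two-sample t-test at 0.05: 14 per group needs d = 1.273.

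Neither value can be taken as the study's effect size, so standardised differences are assumed below and shown over a range.

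**2. Per-pair level.** Pairs = 4 × 3 / 2 = 6; 0.05/6 = 0.0083. Three pairs include MA.

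**3. Conservatism.** Simulating four equal groups of 20 with normal data, equal SD and pooled error, the chance that six-pair Bonferroni rejects at least one pair is 0.041, below the permitted 0.05.

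**4. Power of one contrast under Bonferroni.** Noncentral t with 4n − 4 degrees of freedom and noncentrality d × √(n/2). For n = 20 and d = 0.8: df = 76, noncentrality = 0.8 × √10 = 2.53, critical t = 2.709, power = 0.43.

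| d | 20 per group | 14 per group |
|---|---|---|
| 0.6 | 0.22 | 0.14 |
| 0.8 | 0.43 | 0.28 |
| 1.0 | 0.67 | 0.47 |
| 1.2 | 0.86 | 0.67 |
| 1.273 | 0.90 | 0.73 |
| 1.5 | 0.98 | 0.88 |
| 2.0 | 1.00 | 0.99 |

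**5. What Holm does.** Sort the six p-values. Compare the smallest with 0.05/6 = 0.0083, the next with 0.05/5 = 0.0100, then 0.0125, 0.0167, 0.025 and 0.05, stopping at the first failure. No threshold is below 0.0083, so every Bonferroni rejection is also a Holm rejection. The family-wise error remains at most 5%.

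**6. Power under Holm.** Simulation, 100,000 data sets per pattern, 20 per group, means in SD units relative to MA. Each pattern is an assumption.

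| YA | YS | ES | MA-ES, Bonferroni | MA-ES, Holm |
|---|---|---|---|---|
| +2.5 | +0.8 | −0.8 | 0.43 | 0.67 |
| +2.5 | 0 | −0.8 | 0.43 | 0.57 |
| 0 | −0.8 | −0.8 | 0.43 | 0.48 |
| 0 | 0 | −0.8 | 0.43 | 0.46 |

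In the first row MA-YS, also 0.8 SD, gains equally (0.43 to 0.67). The upper limit for any d = 0.8 contrast is its unadjusted power of 0.70 (0.705), approached only when all other pairs are rejected first. When every contrast is 2 SD or more, both rules give power near 1.

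**The case against.** **All-pairs Bonferroni after a four-group ANOVA is a legitimate choice.** This stands. Family-wise error within a parameter is controlled, the study is described as descriptive, and nothing in 4.8 is wrong or contradictory. The point is one of efficiency.

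**The loss may be small where it matters most.** This partly stands. If 14 per group came from a two-sample t-test, the implied d is about 1.27, and six-pair Bonferroni with all 20 men retained still gives 0.90. With 14 completers it gives 0.73. The documents give no effect size, so the loss cannot be fixed for any one parameter. Cohen's d will also be reported, so a moderate difference would not disappear from view.

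**A reader might infer that half the alpha is spent on pairs outside the aim, and that only the three MA contrasts should be tested, for instance by Dunnett's procedure.** The arithmetic is right (3 × 0.0083 = 0.025), and Dunnett would raise power at d = 0.8 from 0.43 to 0.56 with 20 per group. The documents do not support the inference. The Introduction makes the effects of ageing and of activity level an objective. YS-ES addresses ageing in sedentary men and YA-YS addresses activity in the young; only YA-ES, which mixes the two, has no clear use. Removing those tests would trade one stated objective for another.

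**A reader might also infer that, with no deciding contrast named, any of six results could be promoted as the main finding.** Correcting over all six pairs protects against this within a parameter. Ranking the contrasts is detail that a full protocol or analysis plan may hold.

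**Holm does not address multiplicity across the many parameters.** True, and neither does Bonferroni within each parameter. Because Holm rejects more, it may also add some false positives across parameters; the 5% guarantee is per parameter under both rules.

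**Conclusion.** The single-step Bonferroni rule in 4.8 is valid but needlessly conservative. Holm's procedure gives the same within-parameter guarantee, keeps all six tests and never rejects fewer hypotheses. For an MA contrast of 0.8 SD with 20 per group, the gain is about 5 to 24 points (0.43 to between 0.48 and 0.67) when several other differences are present. It is about 3 points when only one group differs from the rest, and near zero when all contrasts are 2 SD or more.

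These figures assume normal data, equal SDs, pooled ANOVA error, two-sided testing and illustrative means, because the documents supply no effect size or SD. They also take six pairs as the intended family. This is a low-cost improvement, not an error that threatens the study's conclusions.

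**What to change.** In 4.8, replace the Bonferroni post hoc correction with a Holm step-down adjustment of the six pairwise p-values within each measured parameter, at a two-sided family-wise 0.05, using the pooled ANOVA error. Stating the six pairs also removes the need to infer them.

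Optionally, add that MA-ES, MA-YA and MA-YS in VO2peak are the primary comparisons, which ties the analysis to the aim in the Introduction. The other three pairs keep their formal tests.

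Cost: a change of wording, with no extra participants or measurements. The p-values have to be sorted by hand or by script. Simultaneous confidence intervals that match Holm's decisions are less simple than Bonferroni intervals, so the text should say which intervals are reported and that they may not agree exactly with the adjusted tests.

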Some authors suggested that master athletes represent a sample, which may be considered an “across the life span” and could be a feasible model to estimate healthy human aging [6]. In endurance sports, the physical fitness changes are evaluated mainly by cardiorespiratory fitness (CRF) testing. The CRF reflects the overall capacity of the cardiovascular and respiratory systems [7], which is measured, for instance, through maximal or peak oxygen consumption (VO_2_max). CRF could be assessed by various parameters, however, the VO_2_max is considered as a golden standard [8]. There is a linear relationship between the decline in the endurance performance and the Vo2 max in master athletes [9,10]. In addition, VO_2_max is also a predictor of cardiovascular disease and all-cause mortality [11]. The age-related decline in the VO_2_max across the lifespan is reported to be 5–10% per decade and is accelerated to more than 20% at ages over 70 years in untrained individuals [12]. In master endurance athletes, the proportion of decline can be reduced by maintaining the combination of high-intensity and volume of training up to the age of 70 years [13]. As in the general population, a significant acceleration of the decline in the VO_2_max is present in master athletes after reaching the age of 70 occurs [10]. A decrease in the CRF is caused not only by changes at the levels of the central factors such as maximal heart rate, stroke volume, and an A-V O_2_ difference which are well-documented [9], but also changes in the peripheral factors have significant effects on the decreasing CRF.

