### 2.4. Subjects

The study will involve a total of 80 healthy male subjects divided into four groups (n = 80): group 1, endurance-trained runner athletes (young athletes—YA; n = 20, age range 20–30 years); group 2, adults less active than recommended (young sedentary—YS; n = 20, age range 20–30 years), group 3, master endurance running athletes (master athletes—MA; n = 20, age range 65–75 years); group 4, seniors less active than recommended (elderly sedentary—ES; n = 20, age range 65–75 years, respectively). The groups of young and master endurance-trained runner athletes will only consist of the active marathon runners.

Subjects must meet the following inclusion criteria to participate in this study:(a)for athletes’ groups:
defined as more than 300 min per week of running activity which is, by ACSM [8], considered as vigorous intensity of endurance activity.Both groups must regularly participate in running competitions (in 10 km, half, and full marathon) for young athletes for at least 3 years and for master athletes for at least 25 years.Have a personal best on 10 km run in last season under 35 min in YA group and under 55 min in MA.(b)for groups less active than recommended: no history of regular physical activity training and no more practice than 150 min of moderate or 75 min of vigorous intensity per week.

The standard inclusion criterion for every group will be body mass index (BMI) (range 18.5–30 kg/m^2^).

Exclusion criteria will be recent or current infection, physical disabilities, malignant disease, cardiovascular, metabolic, autoimmune diseases, malnutrition, and pharmacological interference (e.g., steroids, nonsteroidal anti-inflammatory agents, immunosuppressive and antineoplastic drugs). Moreover, the use of performance-enhancing drugs in the past and during the study period is exclusionary.

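### The four groups form a 2×2 age-by-training layout, but the one-way ANOVA gives only pairwise differences: no main effects and no test of whether the age gap differs between runners and less active men

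*Protocol article*

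**What the plan says.** Section 2.4 (Subjects) defines the four groups:

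- YA: "group 1, endurance-trained runner athletes (young athletes—YA; n = 20, age range 20–30 years"
- YS: "adults less active than recommended (young sedentary—YS; n = 20, age range 20–30 years"
- MA: "master endurance running athletes (master athletes—MA; n = 20, age range 65–75 years"
- ES: "seniors less active than recommended (elderly sedentary—ES; n = 20, age range 65–75 years"

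The second specific objective in section 1 (Introduction) is: "To determine the effects of aging and the physical activity level on the measured parameters". The primary aim, in the same section, sets master athletes against elderly less active men, young less active men and young runners.

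Section 4.8 (Data Analysis and Management) gives the group analysis: "A one-way ANOVA with Bonferroni post hoc correction will be used to determine differences between the groups in all measured parameters". It adds Cohen's d for between-group differences, Pearson correlations for associations, and a significance level of 0.05. It names no two-way model, factorial contrast or interaction, and does not say which pairs the post hoc step covers.

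**The concern.** The groups are every combination of two factors, age band and training status, in equal numbers. An objective about the effects of ageing and of activity level is naturally answered by the two factor effects, and by whether one depends on the other. A one-way ANOVA treats the four cells as unrelated labels. Its omnibus test says only that some means differ, and its follow-up gives separate pairwise differences.

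Two things are lost. First, each age or training comparison uses 20 against 20 at a corrected level, where the factorial main effect uses 40 against 40 at 0.05. Second, no test addresses whether the age gap differs between runners and less active men. Anyone wanting to comment on that would have only the observation that one age comparison is significant and the other is not. That is not a test of the difference between them.

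The method is named in the article for every measured parameter. This is therefore not a detail left to an unseen analysis plan: a fuller plan would have to depart from the sentence in section 4.8 to repair it.

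**Working it through.** **Layout (section 2.4).**

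| | Runners | Less active |
|---|---|---|
| 20–30 years | YA, n = 20 | YS, n = 20 |
| 65–75 years | MA, n = 20 | ES, n = 20 |

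**The plan's own figure.** Section 2.3 states 14 per group at power 0.9 and recruits 20. It gives no numerical effect size, so 14 cannot be reproduced. Working backwards, 14 per group corresponds to:
- f of about 0.52–0.54 for the one-way ANOVA;
- d of about 1.27–1.33 for a plain two-sample t test;
- d of about 1.53–1.60 for one pair corrected for six, with pooled variance.

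**Inputs below.** n = 20 per group (section 2.3), two-sided 0.05 (level from section 4.8, sidedness assumed), equal SDs (assumed), residual df = 80 − 4 = 76. Effects in SD units are assumptions. Power comes from the noncentral t distribution.

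**Standard errors, in units of the SD.**
- Main effect (40 against 40): √(1/20) = 0.224
- One pair (20 against 20): √(2/20) = 0.316
- Interaction, (YA − MA) − (YS − ES): √(4/20) = 0.447

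**Power for an age or training effect.** At 0.8 SD the noncentrality is 0.8/0.224 = 3.58 for the main effect and 0.8/0.316 = 2.53 for a pair. The critical values are 1.99 at 0.05, 2.71 at 0.05/6 and 2.56 at 0.05/4.

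| Assumed effect | Main effect | One pair, six corrected | One pair, four corrected |
|---|---|---|---|
| 0.6 SD | 75% | 22% | 26% |
| 0.8 SD | 94% | 43% | 49% |
| 1.27 SD | >99% | 90% | 92% |
| 1.5 SD | >99% | 98% | 98% |

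**How often the pairs mislead when there is no interaction.** Let the age decline be the same in both strata, and let P be the power of one pair with six corrected. The YA–MA and YS–ES comparisons use different men, so the chance that the sedentary pair is significant and the athlete pair is not is roughly P(1 − P). The exact value is slightly lower because the two share a variance estimate; it was simulated.

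| Age effect in both strata | P(1 − P) | Simulated |
|---|---|---|
| 0.8 SD | 0.434 × 0.566 = 0.25 | 24% |
| 1.0 SD | 0.674 × 0.326 = 0.22 | 21% |
| 1.27 SD | 0.901 × 0.099 = 0.09 | 9% |
| 1.5 SD | 0.977 × 0.023 = 0.02 | 2% |

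The reverse pattern is equally likely. A direct interaction test at 0.05 gives a false positive in 5% throughout.

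**Power of the interaction at 20 per group.** The noncentrality is D/0.447 for a difference of differences D. Power is 20% at 0.5 SD, 42% at 0.8 SD, 60% at 1.0 SD and 80% at 1.27 SD (1.27/0.447 = 2.84); 90% needs 1.47 SD. With 14 per group, 80% needs 1.53 SD.

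**The case against.** The strongest reply is that the plan already tests age and training. A reader might infer that these effects are never tested, and that is wrong. MA against YA and ES against YS are age comparisons within a training level; MA against ES and YA against YS are training comparisons within an age band. The post hoc step can supply all four. What is absent is the overall effect of each factor and the interaction.

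A reader might also infer that the study's main question is whether running slows ageing. The primary aim is worded as comparisons of master athletes with three other groups, and no listed objective states the interaction as its question. Slower ageing appears in the abstract as background on recommended activity. Nor does the article say that its authors will contrast significant with non-significant pairs. The plan leaves them no formal test for that statement, but it does not commit them to making it.

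The reply is also right on size. The effects of 0.6 to 1.0 SD are assumed. The effects of roughly 1.27 to 1.60 SD implied by 14 per group would give a single pair 90% power or more at 20 per group, and the misleading pattern then falls to 9% or less. The power figures also compare an effect averaged over both strata with one inside a single stratum, which are different quantities. Correction over all six pairs is inferred, although correcting four instead raises power at 0.8 SD only from 43% to 49%.

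None of this supplies the missing tests. The one-way model gives no main effect and no interaction at any effect size.

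**Conclusion.** The point holds in limited form. The design is a balanced 2×2, the second objective is about its two factors, and the named analysis ignores that structure. Simple age and training differences are tested; factorial main effects and the age-by-training interaction are not.

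The cost depends on effect sizes that the article does not give. At 0.8 SD a main effect would have 94% power against 43% for one of six corrected pairs. The one-directional misleading pattern runs from about 24% of studies at 0.8 SD to 2% at 1.5 SD. These figures assume 20 completers per group, equal SDs and, for the pattern, correction over six pairs.

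A reader might infer that an interaction test would settle whether running slows ageing. It would not. Section 2.1 describes a cross-sectional study. Section 2.4 sets different entry criteria for the two runner groups: 10 km under 35 minutes and at least 3 years of competition for the young, under 55 minutes and at least 25 years for the masters. The interaction would show that the age gap differs by training status, part of which could reflect those criteria.

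**What to change.** In section 4.8, replace the one-way ANOVA for continuous parameters, at least for VO2peak, by a two-way ANOVA with age, training and age × training. Report both main effects and the interaction with 95% confidence intervals.

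Keep Bonferroni-corrected pairwise contrasts as follow-up and list them. The primary aim names MA against ES, YS and YA; the second objective adds YS against ES and YA against YS. MA against YS differs in both factors but must stay, because the aim names it. If those five are the list, each is tested at 0.05/5 = 0.01.

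State two limits in the text: the interaction has 80% power only for about 1.27 SD at 20 per group, and it describes a difference in age gaps without proving slower ageing. An unclear interaction should be reported through its interval and not read as equal gaps.

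The Introduction expresses decline in relative terms ("The age-related decline in the VO_2_max across the lifespan is reported to be 5–10% per decade"), and equal percentage declines from different starting levels are unequal absolute declines. An interaction on log VO2peak could therefore be added as a sensitivity analysis. It need not become the primary test, for which the study has not been sized.

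The cost is a change of analysis wording, with the same data and software.

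### Pooled-variance ANOVA with Bonferroni pairs is fixed for every parameter; if group spreads differ, individual pairwise tests have the wrong error rate and power, although the familywise rate stays near 0.05 with equal groups

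*Protocol article*

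**What the plan says.** Section 4.8 (Data Analysis and Management) names a single method for group comparisons: "A one-way ANOVA with Bonferroni post hoc correction will be used to determine differences between the groups in all measured parameters". The parameters include the primary outcome, VO2peak on the cycle ergometer (section 3), ELISA inflammatory markers and hormones (4.6), and PCR gene expression and electron-microscopy counts and percentages (4.7).

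Checks come before the analysis: "Data will be assessed for normality and homogeneity to ensure that the analysis’ assumptions will be met". The tools are two formal tests, Shapiro–Wilk for normality and Levene for equal variances, together with graphical inspection. No other analysis is attached to a failed check. The significance rule is "The results will be considered significant for values of <0.05", and the software is named: "Data analysis will be performed using the SPSS 23".

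Section 2.3 plans equal groups: "with a mean effect size and a power of 0.9, the sample size of 14 participants per group would be needed", raised to 20 per group to allow for dropout. No standard deviation is given for any group or parameter.

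**The concern.** The study's objectives are answered by particular pairs, such as master athletes against elderly sedentary men or against young athletes, more than by the overall F test. A pooled Bonferroni test gives every pair the same error variance, the average over all four groups. If the groups differ in spread, that average is too small for two wide groups and too large for two narrow ones. Wide pairs then give too many false positives, and narrow pairs lose power.

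Different spreads are plausible in this design. The groups are about 45 years apart in age, and the athletes enter by different 10 km limits ("under 35 min in YA group and under 55 min in MA"), while the sedentary groups have an activity ceiling but no performance limit. The planned checks can flag the problem, but the text does not say what would then change.

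**Working it through.** **Inputs.** From the article: four groups, 20 planned per group, 14 stated as sufficient, alpha 0.05. Assumed: normal data, SD ratios of 1.5 and 2, two-sided pairs, Levene at the 0.05 level.

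**The plan's own figure.** The article gives no error rate or power for the pairs. Its 14 per group at power 0.90 corresponds to Cohen's f of about 0.52 in a four-group F test. As no numerical effect size is stated, 14 can be neither confirmed nor refuted, and this point does not depend on it.

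**Nominal level.** Four groups give 4 × 3 / 2 = 6 pairs, so 0.05 / 6 = 0.0083 per pair. With 80 − 4 = 76 degrees of freedom the critical t is 2.71.

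**Hand calculation, 20 per group.** With equal groups the pooled variance averages the four group variances. For a pair (i, j), let r = √[(σi² + σj²) / (2 × pooled variance)]. The pooled test then behaves like a correct test with critical value 2.71 / r.

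- SDs 1, 1, 1.5, 1.5: pooled variance (1 + 1 + 2.25 + 2.25) / 4 = 1.625.
  - Wide pair: r = √(2.25 / 1.625) = 1.18; critical value 2.30; error about 0.024.
  - Narrow pair: r = √(1 / 1.625) = 0.784; critical value 3.45; error about 0.0009.
  - Mixed pair: (1 + 2.25) / (2 × 1.625) = 1, so the error is nominal.
- SDs 1, 1, 2, 2: pooled variance (1 + 1 + 4 + 4) / 4 = 2.5.
  - Wide pair: r = √(4 / 2.5) = 1.26; critical value 2.14; error about 0.035.
  - Narrow pair: r = √(1 / 2.5) = 0.632; critical value 4.28; error about 0.0001.

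Power for a 1.2 SD difference between the narrow groups: the expected statistic is 1.2 × √(20 / 2) = 3.79. At ratio 1.5, P(Z > 3.45 − 3.79) is about 63%. At ratio 2, P(Z > 4.28 − 3.79) is about 31%; simulation, which lets the pooled variance vary, gives 33%.

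**Simulation, two narrow and two wide groups, 20 each.**

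| | Ratio 1.5 | Ratio 2 |
|---|---|---|
| Wide null pair, pooled | about 0.025 | 0.036 |
| Narrow null pair, pooled | 0.0009 | 0.0001 |
| Narrow-pair power at 1.2 SD, pooled | 63% | 33% |
| Same, Welch pairs with Bonferroni | 83% | 83% |
| Same, Games-Howell | 86% | 86% |
| Overall F, null | 0.054 | 0.062 |
| Familywise rate, pooled Bonferroni | 0.046 | 0.054 |
| Levene detects | 45% | 90% |

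With only one wide group, F is 0.056 (ratio 1.5) or 0.067 (ratio 2), and the familywise rate 0.047 or 0.058. With 14 per group, two wide, Levene detects ratio 1.5 in about 30% of studies and ratio 2 in about 74%.

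**Unequal groups after dropout.** Sizes 20, 20, 14, 14 with SDs 1, 1, 2, 2: F 0.093, familywise 0.083. If the larger groups are the wider ones (14, 14, 20, 20), F is 0.043 and the familywise rate 0.036.

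**Alternatives.** Welch's ANOVA stays at 0.049-0.051 over the scenarios run. Games-Howell holds the familywise rate at 0.048-0.053. Under equal variances its power for 1.2 SD is 85.8% against 85.7% for pooled Bonferroni at 20 per group, and 66.1% against 66.7% at 14.

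**Skewed markers (assumed lognormal, log-SD 1, 20 per group, one group shifted by 1 log-SD).** Upward shift: power about 58% on the raw scale and 68% on the log scale. Downward shift: 18% raw and 67% log. With four identical groups the raw-scale F rejects at 0.039 and the familywise rate is 0.029, so there is no excess of false positives.

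**The case against.** The strongest reply is that this is only missing detail. The article checks normality and homogeneity first, and what follows a failed check is normally left to a statistical analysis plan or full protocol, neither of which is shown. That is fair as far as it goes: the absence of a stated fallback is not in itself an error. What remains is that the stated rule assigns one method to every parameter, and a default exists that performs better at almost no cost.

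Three stronger readings are tempting, and the documents do not support them.

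- A reader might infer that any parameter with unequal spread gets wrong error rates throughout. With equal groups of 20 and ratios up to 2, the overall F (0.054-0.067) and the familywise rate (0.046-0.058) stay close to 0.05, and mixed pairs are nominal when two groups are wide. Bonferroni is meant to control the familywise rate, and here it nearly does.
- A reader might infer that Levene's test will usually miss the problem. That holds at ratio 1.5. At ratio 2 with 20 per group it misses only about 10%, and histograms and Q-Q plots are planned as well.
- A reader might infer from the 35 and 55 min limits that VO2peak has unequal spread. Those limits concern running time, whereas the outcome is measured on a cycle ergometer, and the sedentary groups are restricted too, by activity, BMI and health criteria. No SD ratio follows.

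Part of the gain from 83% to 86% comes from Games-Howell being less conservative than Bonferroni, not from its handling of variance. The like-for-like comparison for unequal spread is 63% or 33% against 83%.

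**Conclusion.** The point holds for the individual pairwise tests. If spreads differ by a factor of 1.5 to 2, the wide pair's error is about three to four times nominal (0.025 / 0.0083 = 3.0; 0.036 / 0.0083 = 4.3), and power in the narrow pair drops from about 86% to 63% or 33%. It does not amount to a general failure of error control: clear familywise inflation (about 0.083 at ratio 2) appears when dropout leaves the wider groups smaller.

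Everything rests on assumed SD ratios and normal data. The documents do not show which parameters, if any, are affected, and harm to the VO2peak contrasts in particular is possible, not demonstrated. Skewness of the assay markers is also assumed, and its harm is lost power, not false positives. This is a cheap improvement to the stated method, not a flaw that invalidates the study.

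**What to change.** In section 4.8, make Welch's ANOVA with Games-Howell pairwise comparisons the default for all group comparisons, and do not make the choice depend on Levene's test. Such a gate gives little protection: with sizes 20, 20, 20, 14 and SDs 1, 1, 1, 2, the F test still rejects a true null in about 12.6% of the studies that pass Levene. The histograms and Q-Q plots can stay as description.

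Add that right-skewed ELISA and PCR markers are analysed on the log scale and reported as ratios of geometric means.

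The cost is about two sentences and slightly more analysis work. If variances are in fact equal, Games-Howell loses under 1 percentage point of power; Welch pairs with Bonferroni would lose about 2-5 points.
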